## Abstract

*

Streptococcus pyogenes

* (also known as group A *

Streptococcus

*, Strep A) is an obligate human pathogen with significant global morbidity and mortality. Transmission is believed to occur primarily between individuals via respiratory droplets, but knowledge about other potential sources of transmission via aerosols or the environment is limited. Such knowledge is required to design optimal interventions to control transmission, particularly in endemic settings. We aim to detail an experimental methodology to assess the transmission potential of Strep A in a clinical environment. We will examine potential sources of transmission in up to 20 participants recruited to the Controlled human infection for penicillin against *
Streptococcus pyogenes* (CHIPS) Trial. Three approaches to understanding transmission will be used: the use of selective agar settle plates to capture possible droplet or airborne spread of Strep A; measurement of the possible distance of Strep A droplet spread during conversation; and environmental swabbing of personal and common high-touch items to detect the presence of Strep A on hard and soft surfaces. All methods are designed to allow for an assessment of transmission potential by symptomatic, asymptomatic and non-cases. Ethical approval has been obtained through Bellberry Human Research Ethics Committee (approval 2021-03-295). Trial registration number: ACTRN12621000751875. Any results elicited from these experiments will be of benefit to the scientific literature in improving our knowledge of opportunities to prevent Strep A transmission as a direct component of the primordial prevention of rheumatic fever. Findings will be reported at local, national and international conferences and in peer-reviewed journals.

## Data Summary

No data were generated or reused in the research.

Impact StatementThis proposed investigation provides a nascent opportunity to conduct experimentation regarding the transmissibility of Strep A bacteria, a pathogen causing significant global infection, illness and death. To date, questions remain as to how Strep A can spread from person to person, with emerging research implicating routes such as airborne and small droplet. We outline three experiments occurring alongside the Controlled human infection for penicillin against *
Streptococcus pyogenes* (CHIPS) Trial whereby participants will be purposely challenged with Strep A and given different doses of penicillin, with the aim of determining the minimum dose required to prevent the development of Strep A pharyngitis. Any results obtained from these experiments will be of benefit to the scientific literature in improving our knowledge of Strep A prevention opportunities.

## Introduction

*

Streptococcus pyogenes

* (Group A *

Streptococcus

*, Strep A) is an obligate human pathogen with no known animal or environmental reservoir [1]. Strep A infections present with diverse clinical phenotypes, including superficial (i.e., pharyngitis, impetigo) and invasive (i.e., bacteraemia, necrotizing fasciitis) infections [2, 3]. Globally, Strep A is estimated to cause over 162 million cases of impetigo (skin sores) at any one time, 616 million cases of acute pharyngitis (sore throat) per year and 177, 000 deaths due to invasive disease [4]. This burden is exacerbated by the potential for Strep A infection to cause delayed, immune-mediated conditions, such as acute rheumatic fever (ARF) and rheumatic heart disease (RHD), which constitute significant morbidity and mortality even with treatment [5]. Estimates suggest 471, 000 cases of ARF annually, with 40 million people presently affected by RHD and 340,000 annual deaths [6]. This array of clinical manifestations places Strep A in the top 10 most prevalent pathogens globally [3, 7, 8].

Although most cases of pharyngitis are caused by respiratory viruses [9], Strep A is the primary cause of bacterial pharyngitis, isolated in 10–40 % of cases in children [10]. Colloquially known as ‘Strep throat’, symptoms include pain when swallowing, a temperature over 38 °C, swollen tonsils and tonsillar or pharyngeal exudates [11]. To date, Strep A remains reliably sensitive to penicillin, which is the cornerstone of treatment [12]. First-line treatment is oral penicillin therapy for 10 days or one injection of intramuscular benzathine penicillin [11]. Given the lower rate of bacterial pharyngitis compared with viral pharyngitis and resolution of symptoms for most pharyngitis without treatment, prescription of antibiotics without confirmation of Strep A by throat swab is only recommended for those at high risk of Strep A immune-mediated diseases [13]. In Australia, this includes Aboriginal and Torres Strait Islander people, who are at high risk of ARF and RHD [13].

Existing evidence points to the transmission of Strep A primarily by large respiratory droplets [14–16]. Contemporary methods have worked to verify this and through the use of biological swabs, environmental swabs and environmental settle plates have suggested other mechanisms, including small droplet (nasal secretions, sputum or spit) [17, 18], skin-to-skin contact [19, 20], direct contact with bedding, fabrics and surfaces [21, 22], and via food [23, 24] and insects [25–27]. A study completed in the United Kingdom (UK) during a recent scarlet fever outbreak suggested the potential for Strep A to be disseminated via the airborne route, as measured by the placement of settle plates at various heights above the droplet-generating potential of small children [28]. Research in clinical settings has also used settle plates to identify transmission during outbreaks of Strep A causing invasive disease [29]. While verification of many of these transmission mechanisms is still required, it is acknowledged that the type of spread from infected to uninfected individuals may vary according to the clinical manifestation of infection [30].

This protocol, embedded in a human challenge study evaluating the minimum concentration of penicillin required to prevent pharyngitis infection [31], defines the experimental methodology we designed to further understand the transmission potential of Strep A pharyngitis in a controlled setting.

## Method and analysis

### Study design

This sub-study forms a component of the Controlled human infection for penicillin against *
Streptococcus pyogenes* (CHIPS) Trial, (registration number ACTRN12621000751875), a double-blind, placebo-controlled, randomized trial using a previously described human challenge model [31]. Briefly, the CHIPS Trial is designed to determine the optimal dose of penicillin needed to prevent Strep A pharyngitis, conducted in a purpose-built research facility resembling a hospital ward managed by a contract research organization (CRO). All potential participants undertake screening throat swabs and a serum *emm*75 type-specific serology to exclude Strep A carriage or prior infection with the same strain. Each participant is then randomized to receive one of five doses of steady-state penicillin infusions – 0 (placebo), 3, 6, 12 and 20 ng/mL – prior to receiving a direct oropharyngeal challenge with an inoculum of the *emm*75 strain of Strep A via a ‘reverse’ throat swab [32, 33]. Participants are then monitored for development of Strep A pharyngitis according to pre-specified outcome criteria during a confinement period lasting up to 6 days. All participants will be treated as possible infections. This sub-study involves three separate – but related – experiments (detailed below).

### Study objectives

The primary objective of this sub-study within CHIPS is to assess the transmission potential of Strep A in a clinical environment, where the timing and infective dose of Strep A causing potential pharyngitis are pre-defined. Secondary objectives include determining the distance of Strep A droplet spread during conversation, investigating potential airborne spread of Strep A, and the isolation of Strep A from hard and soft surfaces in the clinical environment. It is also anticipated that this sub-study may allow for determination of the impact of different doses of treatment with penicillin against the transmission potential of Strep A.

### Sample size

The CHIPS Trial will be recruiting 60 participants as dictated by sample size calculations [31]. For this pilot sub-study, a formal sample size calculation has not been performed. Instead, a pragmatic approach dictated by resource and personnel constraints has been adopted and up to 20 participants will be enrolled. All participants will consent to participate in the sub-study at the time of trial enrolment and will provide verbal consent to participation at the first time point (24 h post-challenge).

### Study procedures

**1. The capture of environmental Strep A in the vicinity of a potential infection**

Experiments will be completed at three timepoints: 24, 36 and 48 hours following inoculation of the participant with Strep A (the challenge, Day 1). Prior to inoculation, one removable adhesive shelf will be placed on a solid wall 2 metres above the floor in each of the participant’s inpatient cubicles. At 09 : 00 on Day 2 (24 hours post-challenge) one horse blood agar containing colistin and nalidixic acid (HBA-CNA, Pathwest, WA, Australia) selective settle plate will be placed on each shelf and another on the overbed tables of participants. HBA-CNA settle plates that allow Strep A growth and minimize the overgrowth of swarming Gram-negative bacteria will be used throughout [34]. These will remain in position for 4 hours and be removed at 13 : 00. This same process will be repeated on Day 3 (48 hours post-challenge). Settle plates will also be placed in the same positions described above whilst participants are sleeping (approximately 36 hours post-challenge). These will be placed at 22 : 00 on Day 2 (~36 hours post-challenge) and remain in place for 8 hours, before removal at 06 : 00 on Day 3.

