**2. The distance that Strep A droplets move beyond a suspected infection**

These experiments will be completed at two time points: 24 hours post-challenge and 48 hours post-challenge, commencing at 09 : 00 on Days 2 and 3, respectively. Participants will be seated on their beds in front of a table draped with a sterile mat and adjusted to be the same height as their chest. The table will be exactly 30 centimetres (cm) from the chest of the participant and will hold the HBA-CNA settle plate (Fig. 1). To understand transmission during speaking, the participant will be asked to count upwards from one in a conversational tone for one minute as recorded by a stopwatch. At the conclusion of the minute, the participant will cease counting, and the plate will remain in place for an additional minute to capture any droplets that may still be falling. The experiment will be repeated in the manner described above with new plates placed at distances of 90 and 180cm [14, 28].

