**3. The environmental assessment of the confinement room via swabbing**

Following the completion of the droplet transmission experiments, environmental swabs of five items belonging to each participant will be collected. These will include one personal item as determined by the participant, the bed remote control, bedside table, water bottle/cup and intravenous (IV) stand. Flocked swabs (Conan regular flocked swab breakpoint in peel pouch sachet; Copan, Italy) selected for appropriateness of use and transport with our selected medium will be moistened with two to three drops of sterile saline and rolled over the selected object/surface in at least two different diagonal directions across a surface area of approximately 25 cm^2^. Swabs will be placed immediately in a cryovial containing 0.5 ml of skim milk, glucose, glycerol broth (SGGB) solution (PathWest Media) kept at 4–8 °C. In addition, 10 common, high-touch areas in the confinement room will be swabbed using the same methodology, selected based on observation of the room during morning vital checks. A timeline demonstrating when each experiment will occur can be seen in Fig. 2.

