### Microbiological analysis

All swabs and CNA plates collected will undergo transfer and processing for microbial culture for beta-haemolytic streptococci (BHS) using gold standard culture methodology [35] and according to Clinical and Laboratory Standards Institute (CLSI) standards. If no bacterial growth is observed after 24 hours, incubation will be extended for a further 24 hours to allow growth of slow-growing or small colonies. The presence of Strep A as indicated by β-haemolytic morphology will be confirmed with subculture, bacitracin sensitivity testing and positive group A latex agglutination reaction (Streptex, Thermo Scientific). Strep A isolates will be stored at −80 °C to permit further strain characterization. Results will be reported as the presence or absence of Strep A on each sample. Quantitation of the amount of Strep A is not possible with this experimental design.

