This above point is, however, a limitation of the methodology, with contamination a possibility. Individual participants are the only ones with access to their belongings swabbed in experiment 3, so the authors believe there to be limited chance of cross-contamination between participants. As participants keep their curtains closed droplet contamination is unlikely on any plates, but potential airborne spread remains a possibility. This is also possible with the overbed plates placed at a height of 2 metres. As all participants are being given the *emm75* strain of Strep A, the only way to confirm contamination is if the samples of a participant are positive for Strep A despite no nasal or throat samples being taken from the participant confirming this. Symptomatic assessment will also be referred to should this occur.

These experiments have several limitations. Firstly, it is a small pilot study of only 20 participants due to resource and personnel constraints. However, this is the first time similar experiments have been conducted to improve our knowledge of Strep A transmission in more than 70 years. Participants receive a placebo or varying concentrations of penicillin infusion, which may reduce the likelihood of Strep A inoculating the agar settle plates or surface swabs. This limitation is overcome by inclusion of a placebo and all participants being inoculated with the same standardized dose of *emm*75. There is a possible limitation in restricting the distances in experiment 2 to 180 cm; however limitations of space in the confinement facility prevented further extension of this experiment without potentially exposing staff and other participants. Further, the CRO deemed asking challenged participants to cough or sneeze at these distances to be an unacceptable level of exposure risk to others; thus, talking was selected as an appropriate intermediary. Finally, time and resource constraints have limited the use of more specialized equipment – such as microbial air samplers – to determine the influence of factors such as airflow and air exchange rate [40] in this study, although the research team are presently investigating the possibility of employing such methods in households where the burden of Strep A is high. The results from this sub-study will of necessity precede the development of future protocols.

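### With no environmental sample before challenge and no strain typing in the outcome, background Strep A cannot be told from challenge shedding in culture-positive participants or on common surfaces

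*Protocol article*

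**What the plan says.** The Protocol article times its three experiments as follows.

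- Experiment 1, settle plates: "Experiments will be completed at three timepoints: 24, 36 and 48 hours following inoculation of the participant with Strep A (the challenge, Day 1". The only step before challenge is mounting an empty shelf: "Prior to inoculation, one removable adhesive shelf will be placed on a solid wall 2 metres above the floor".
- Experiment 2, talking plates: "These experiments will be completed at two time points: 24 hours post-challenge and 48 hours post-challenge".
- Experiment 3, swabs: "Following the completion of the droplet transmission experiments, environmental swabs of five items belonging to each participant will be collected". The shared area is added: "In addition, 10 common, high-touch areas in the confinement room will be swabbed using the same methodology".

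Participants themselves are sampled beforehand (Study design): "All potential participants undertake screening throat swabs and a serum *emm*75 type-specific serology to exclude Strep A carriage or prior infection with the same strain". Nothing comparable is described for the room.

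Under Microbiological analysis, an isolate is confirmed by haemolysis, bacitracin sensitivity and group A latex agglutination, and each sample is reported as Strep A present or absent. On typing, the section says only: "Strep A isolates will be stored at −80 °C to permit further strain characterization". Under Statistical analysis, the present/absent result is set against dose and diagnosed pharyngitis.

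The Discussion acknowledges contamination as a limitation. It notes that all participants receive emm75 and concludes that "the only way to confirm contamination is if the samples of a participant are positive for Strep A despite no nasal or throat samples" confirm it, with symptoms consulted as well.

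**The concern.** The stated attraction of this setting (Study objectives) is that the time and dose of exposure are known. That helps only if a positive plate or swab can be tied to the challenge. Two things would make the link: knowing that the site was negative beforehand, or knowing that the isolate is the challenge strain. The plan includes neither in its outcome.

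The remaining safeguard is the comparison with the participant's own nose and throat samples. It is silent exactly where a positive sample will be read as shedding, in people who are culture-positive. It also has no meaning for a common surface, which belongs to no single participant. The primary objective and the comparison by pharyngitis status depend most on these samples.

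**Working it through.** The plan gives no figure to reproduce: the sub-study has no sample-size calculation and no assumed positivity rate. The check is therefore structural.

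**Samples affected (counts from Study procedures)**

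- Settle plates per participant: 2 positions × 3 times = 6.
- Talking plates per participant: 3 distances × 2 days = 6.
- Item swabs per participant: 5 per round. The text does not settle whether there are one or two rounds, so 5 or 10.
- Total per participant: 6 + 6 + 5 = 17, or 6 + 6 + 10 = 22.
- Common-area swabs: 10 per round, linked to no participant.

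**What each result can show**

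Let s be the chance that a sample is positive through the current participant's challenge shedding, and b the chance that it is positive from any other source, taken as independent. The documents give neither value. The observed chance of a positive is

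p = 1 − (1 − s)(1 − b) = s + b − sb.

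1. Culture-negative participant: s is taken as 0, so p = b. The Discussion check flags these positives.
2. Culture-positive participant: only p is observed. Without a prior sample or a strain type, s and b cannot be separated, and the check flags nothing.
3. Common surface: again only p is observed, and there is no own-throat result to compare with.

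**What follows for the comparisons**

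- By dose, with no positives set aside: the difference between two dose groups is (1 − b)(s₁ − s₂). Background unrelated to dose shrinks a real difference and does not create one.
- By infection status, if flagged positives were set aside: culture-negative participants keep a rate of 0, and culture-positive participants keep s + b − sb. With s = 0 the remaining difference is b, produced by the rule alone. The article does not say that flagged positives would be removed, and Statistical analysis gives no rule either way.

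**What typing would do**

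Split background into non-emm75 (b_o) and emm75 (b₇₅), with 1 − b = (1 − b_o)(1 − b₇₅). Counting only emm75 leaves p = s + b₇₅ − s·b₇₅. The b_o part is gone and b₇₅ stays.

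**Where emm75 residue could matter**

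The plates in experiments 1 and 2 are fresh agar, and experiment 2 also uses a sterile mat. Old surface residue would have to become airborne again to reach them. In experiment 3, one of the five items is personal to the participant. Three (bed remote control, bedside table, IV stand) are ward fixtures by their nature, although the Discussion treats the swabbed belongings as accessible only to the participant. Residue is therefore plausible mainly on those three fixtures and the 10 common sites.

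**The case against.** **The Discussion sentence is about something else.** It opens from the fact that everyone receives emm75 and concerns spread between participants. For that problem typing does not help, and neither would a sample taken before challenge, since a neighbour sheds afterwards. This stands. The sentence is sound for emm75 passing between beds and needs limiting, not reversing. What it leaves out is a source outside the challenge, which a non-emm75 isolate would reveal.

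**Safeguards exist.** A reader might infer that background Strep A is simply counted as shedding, or that nothing at all is sampled before challenge. Neither is supported: participants have screening throat swabs, the Discussion check covers culture-negative participants, and isolates are kept so that typing remains possible. The gap is confined to culture-positive participants and common surfaces.

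**The sources are assumed.** The article does not say that cubicles are reused or that staff carry Strep A, and cleaning between participants may be covered in the full trial protocol. This stands too, and both must be labelled as assumptions.

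**Typing may be in the full protocol.** Possibly, but the article defines the outcome as Strep A of any type and analyses it so. The point concerns that definition, not a missing laboratory detail.

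**A full baseline does not fit the plan.** Common sites are chosen during morning checks, and verbal consent is given at 24 h, so a complete sampling pass on Day 1 would conflict with both. It would also burden a resource-limited pilot of up to 20. This is a good reason not to ask for it.

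**Conclusion.** The point holds in a limited form. No environmental sample precedes challenge and the outcome accepts any group A isolate, so a positive result cannot be attributed to the challenge rather than to background in two places: all 17 (or 22) samples of a culture-positive participant, and all common-area swabs. The Discussion check does not reach either place and is not carried into the analysis.

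These counts show where the ambiguity lies, not how often it occurs. A reader might want to say what share of positives would be background. The documents give no background or deposition rate, so any such percentage would only reflect the rates put in. Nor do they support saying that the dose comparison is biased: dose is randomised and blinded, and background unrelated to dose would mainly dilute a difference.

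The conclusion rests on the written timing in Study procedures (the timeline figure is not shown) and on the outcome as worded under Microbiological analysis and Statistical analysis. It does not depend on cubicle reuse or staff carriage. Those affect only how large the background might be.

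**What to change.** 1. emm-type every environmental isolate already stored at −80 °C. Under Microbiological analysis and Statistical analysis, define the outcome as presence of emm75, and report other types separately as background.
2. In the Discussion, limit the sentence on confirming contamination to emm75 spread between participants, and add that a non-emm75 isolate identifies an outside source.
3. If cubicles are reused (an assumption to be confirmed), choose one of two options. Either swab the three ward fixtures (bed remote control, bedside table, IV stand) before inoculation, or state that positives on fixtures and common surfaces cannot be attributed to the current participant.

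Cost: items 1 and 2 need typing of a probably small number of stored isolates, and a few sentences. There is no new sampling and no participant burden. Typing does not remove emm75 carried over from an earlier participant, which is why item 3 is there. Its swabbing option adds 3 swabs per participant, at most 3 × 20 = 60 in all, by the existing method. The fixtures are already named in the plan and are not personal belongings, so the difficulty with selecting common sites does not arise; the investigators should confirm that the timing of verbal consent is no obstacle. The statement option costs nothing.
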